## Abstract

**Background:**

Endovascular treatment (EVT) is the standard treatment for acute ischemic stroke (AIS) patients with large vessel occlusion (LVO).

**Aims:**

Endovascular Treatment for Acute Ischemic Stroke in China (DETECT2-China) aims to evaluate real-world outcomes and safety of EVT for LVO-AIS patients in China.

**Design:**

DETECT2-China is a prospective, national, multi-center study registered in ClinicalTrials.gov (NCT05092139). This study plans to enroll a total of 3,000 consecutive patients who received EVT for LVO. All eligible patients are adults aged 18 years or older with acute LVO who received EVT and standard medical treatment according to the Chinese stroke guidelines and local practice.

**Outcome:**

The primary outcome is functional independence (modified Rankin Scale score, mRS ≤ 2) at 90 days. The secondary outcomes include (1) the proportion of patients with mRS scores of 0–1 at 90 days, (2) distribution of mRS at 90 days, (3) changes in National Institutes of Health stroke scale (NIHSS) at 24 h, 48 h, and 12 days or discharge (whichever is earlier), (4) the proportion of symptomatic intracranial hemorrhage (sICH) within 48 h, and (5) the proportion of death within 7 days.

**Discussion:**

The DETECT2-China will provide real-world data about the effectiveness and safety of EVT for AIS-LVO patients in China.

## Introduction and rationale

Acute ischemic stroke (AIS) accounts for 60–80% of all stroke cases in China (1). Intravenous thrombolysis has been demonstrated to be associated with favorable functional outcomes for patients with AIS presenting within 4.5 h and is considered Class I evidence in national guidelines (2, 3). However, the efficacy of intravenous thrombolysis alone for patients with acute large vessel occlusion (LVO) is limited, and endovascular treatment (EVT) is often needed (4). Several studies have shown that EVT can achieve a high rate of recanalization and improve the outcome in LVO-AIS patients (4–9), which was further confirmed by the MR CLEAN REGISTRY and SVIN registry in routine clinical practice (10, 11). However, most of these studies were conducted in North America, Europe, and Australia. With the development of stroke centers in recent years, EVT has been performed in many Chinese hospitals. Given the restriction of EVT by equipment, cost, and experienced physicians, due to a different healthcare system in China, and due to the high prevalence of intracranial atherosclerosis (ICAS) in the Chinese AIS population (12), a multi-center, real-world registry study is needed to determine the real-world outcomes and safety of EVT for LVO-AIS patients in China, including imaging evaluation strategies and patient post-procedural management. In this context, this prospective, national, multi-center, real-world registry study is performed to evaluate the effectiveness and safety of the real-world practice of EVT in Chinese patients with LVO-AIS.

## Methods

### Design

Endovascular Treatment for Acute Ischemic Stroke in China (DETECT2-China) is a prospective, national, multi-center, registry study in China and intends to include 30 comprehensive stroke centers (Supplementary material) between January 2022 and December 2024 to characterize the real-world clinical outcomes and safety of EVT for patients with LVO-AIS in China.

### Study population

In the DETECT2-China prospective registry, eligible participants are LVO-AIS patients who received EVT. The detailed inclusion and exclusion criteria are shown in Table 1. To avoid selection bias, all participating centers are obliged to enter consecutive patients undergoing EVT in this study.

**Table 1 T1:** Inclusion and exclusion criteria.

**Inclusion criteria**
•Age ≥ 18 years
•Ischemic stroke confirmed by head CT or MRI and vessel occlusion confirmed by CTA, MRA, or DSA
•Patients receiving endovascular treatment
•First ever stroke or pre-stroke mRS ≤ 2
•Signed informed consent by a patient or their legally authorized representative.
**Exclusion criteria**
•The presence of intracranial hemorrhage at the baseline neuroimaging
•Pre-stroke mRS ≥ 3
•Other serious illness that would confound the clinical outcome at 90 days
•Unavailable neuroimaging data
•Other unsuitable conditions judged by the investigator.

CT, computed tomography; MRI, magnetic resonance imaging; mRS, modified Rankin Scale.

### Standard protocol approval, registration, and patient consent

The protocol of DETECT2-China and data collection have or will have been approved by the Ethics Committee of the General Hospital of Northern Theater Command and all participating sites. All patients are enrolled in the study voluntarily, and patients or their legally authorized representatives sign informed consent. The DETECT2-China trial is registered on www.clinicaltrial.gov (NCT05092139).

### Baseline characteristics

Baseline patient demographics including age, sex, pre-stroke mRS, vascular risk factors, and smoking use will be recorded. Stroke benchmark metrics such as baseline NIHSS, time from last known well, arrival to the hospital, neuroimaging modality and time, and use and time of administration of IVT will be collected. The etiology of the stroke will also be recorded according to the TOAST criteria.

### Intervention

Intravenous thrombolysis with alteplase, tenecteplase, or urokinase can be used before and/or during EVT according to local or national guidelines. Femoral artery or radial artery puncture with local anesthesia is used for EVT. The choice of the anesthetic strategy (conscious sedation or general anesthesia) will be determined by the anesthesiology team and the neurointerventionalist according to a case-by-case basis. EVT will be carried out according to the usual practice of each center, including EVT with stent retrievers, thromboaspiration, balloon angioplasty, stenting, or a combination of these approaches. Intra-arterial thrombolysis with alteplase, tenecteplase, or urokinase and antithrombotic treatment with tirofiban, aspirin, clopidogrel, cilostazol, or ticagrelor are permitted in this registry at the operator's discretion. Systolic blood pressure and diastolic blood pressure will be recorded. Digital subtraction angiography (DSA) and a cone beam CT (or non-contrast CT) will be performed after EVT to evaluate recanalization and exclude intracranial hemorrhage. The number of passes to achieve successful recanalization as well as the use of adjunctive antithrombotics, if pertinent, will be recorded. Recanalization is graded according to the modified thrombolysis in cerebral infarction (mTICI) score, and successful recanalization is defined as having an mTICI grade of 2b-3.

### Outcomes

The primary outcome is the proportion of patients who achieve functional independence (modified Rankin Scale score, mRS ≤ 2) at 90 days. The minimum and maximum values of the modified Rankin Scale score are 0 and 6, respectively; a higher score means a worse outcome with 6 indicating death.

The secondary outcomes include the following: (1) the percentage of patients with excellent functional outcome, defined as an mRS score of 0 to 1 at 90 days, (2) distribution of mRS at 90 days, (3) changes in National Institutes of Health stroke scale (NIHSS) at 24 h, 48 h, and 12 days, (4) proportion of symptomatic intracranial hemorrhage (sICH) within 48 h, defined as an increase in 4 or more points on the NIHSS that is caused by intracranial hemorrhage (ECASS-III definition) (2), (5) proportion of death within 7 days, (6) procedural complications, including vessel dissection, contrast extravasation, embolization into a new territory, femoral access complications, and (7) discharge disposition.

Exploratory outcomes include the following: (1) the association between neuroimaging within 48 h and clinical outcome (neuroimaging includes brain CT, MRI, or DSA); (2) changes in serum biomarkers at 48 h, including matrix metalloproteinases, proinflammatory cytokines, brain-derived neurotrophic factor (BDNF), neurofilament light chain, serum complement C3, C-reactive protein, albumin, copeptin, D-dimer, and uric acid; (3) transcranial Doppler ultrasound data within 24 h, including blood velocity and pulsatility index, which will be collected at some centers; and (4) dynamic changes of cortical blood oxygen saturation by near-infrared spectroscopy within 24 h, which will be collected at some centers.

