### Data management, monitoring, and quality control

All patient data and case report forms will be entered in MedSci (http://DETECT2-China.medsci.cn). The data will be downloaded from MedSci with a dedicated person for statistical analysis. A third-party contract research organization (CRO) and the sponsor will audit the sites regularly to ensure adherence to study documentation, reporting procedures, and study protocol. The registry steering committee is comprised of external scientific advisors and will organize teleconference or in-person meetings to give recommendations about the study. Neuroradiologic assessment will be conducted in a core laboratory. Neuroimaging associated with clinical events will be collected centrally and interpreted by two independent neuroradiologists. An independent Endpoint Events Assessment Committee will adjudicate controversial clinical and imaging outcomes. The trial is initiated and supported by the Cerebrovascular Disease Collaboration and Innovation Alliance (CDCIA) of Liaoning.

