### Statistical analysis

Statistical analyses will be performed based on all enrolled participants or their legally authorized representatives who signed and did not withdraw informed consent. All data will be analyzed with SPSS 23.0 Software. The mean ± standard deviation (SD) will be used if continuous data are normally distributed, and the median and interquartile range (IQR) will be used if continuous data are non-normally distributed. Categorical data are expressed as a number (percentage). Differences between the primary endpoint and secondary endpoints such as mRS (0–1) at 90 days, the proportion of symptomatic intracranial hemorrhage at 48 h, the proportion of intraparenchymal hemorrhage at 48 h, and the occurrence of all-cause mortality at 7 days will be compared using binary logistic regression. The analysis will be adjusted for confounders, including age, sex, baseline NIHSS, pre-stroke mRS, prior stroke, baseline ASPECTS, site of arterial occlusion, transfer of patient, time from last known well, and IVT use (for EVT patients). The 90-day mRS score will be compared using ordinal logistic regression. Change in the NIHSS score will be compared using a general linear model. Time to events of stroke recurrence and other vascular events will be compared using Cox regression. Statistical tests are considered significant when the two-sided *P*-value is < 0.05.

The outcomes in DETECT2-China will be further analyzed by the following subgroups: (1) onset of symptoms to recanalization time (<7 vs. ≥7 h), (2) age (<65 vs. ≥65), (3) NIHSS score on admission (6–16 vs. ≥17), (4) baseline ASPECTS (<6 vs. ≥6), (5) thrombectomy technique (stent retriever vs. contact aspiration or other techniques), (6) anterior circulation vs. posterior circulation, (7) mean systolic blood pressure during the intervention (≤ 120 vs. >120 mmHg), (8) mechanical thrombectomy alone vs. bridging thrombectomy, (9) mothership vs. drip and ship models, (10) stroke etiology (ICAD vs. cardioembolic vs. others), and (11) use of general anesthesia vs. conscious sedation.

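### The sICH definition has no clause for death, so a fatal haemorrhage with no scored post-baseline NIHSS is not counted

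*Protocol article*

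**What the plan says.** The Outcomes section of the protocol article lists the proportion with sICH within 48 h as the fourth secondary outcome and defines it in one clause: "defined as an increase in 4 or more points on the NIHSS that is caused by intracranial hemorrhage", labelled as the ECASS-III definition, with a literature reference. No other route to an sICH classification is printed. The fifth secondary outcome is separate: "proportion of death within 7 days".

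Table 2 schedules the NIHSS at screening, at 24 ± 4 h, at 48 ± 8 h, and at 7 and 12 days. It schedules head CT or MRI at screening, 24 h and 48 h, and adverse events at every visit from 24 h on.

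Under data management, imaging linked to clinical events is collected centrally and read by two independent neuroradiologists. In addition, "An independent Endpoint Events Assessment Committee will adjudicate controversial clinical and imaging outcomes".

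The Statistical analysis section puts sICH at 48 h, intraparenchymal haemorrhage at 48 h and 7-day mortality into adjusted binary logistic regression.

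**The concern.** The rule needs a measured worsening on a neurological scale. A patient who bleeds and dies before anyone repeats the NIHSS has no such measurement, although that course is the most severe form of the event the outcome is meant to capture. A coder who follows the printed wording has to classify this patient as not having sICH.

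sICH is the only intracranial haemorrhage outcome that the Outcomes section defines, so readers will use it to judge the bleeding risk of EVT in this registry. The error runs in one direction, towards a lower rate. It also enters the logistic model as misclassification of the dependent variable. If unscored fatal bleeds are more common in some of the planned subgroups than in others, the comparison between subgroups is affected as well as the overall rate.

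**Working it through.** **Step 1: is there a figure to reproduce?** No. The article states no expected sICH rate, no early fatality rate and no share of fatal bleeds without a scored NIHSS. The check is of the definition; the arithmetic only shows scale.

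**Step 2: apply the printed rule to four kinds of patient.**

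| Course within 48 h | NIHSS rise of at least 4 scored? | Counted as sICH? |
|---|---|---|
| Haemorrhage, survives, rise scored | yes | yes |
| Haemorrhage, rise scored, then dies | yes | yes |
| Haemorrhage, dies with no post-baseline score | no | no |
| Dies of another cause | not from haemorrhage | no, and correctly so |

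Only the third row goes wrong. The definition does not require the rise to be seen at a scheduled visit, so an unscheduled score taken as the patient deteriorates would qualify. The first scheduled post-baseline score is at 24 ± 4 h, so a patient who dies before then depends on an unscheduled one.

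**Step 3: illustrate the size.**

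Inputs:
- planned enrolment N = 3,000 (Sample size determination)
- true sICH rate s = 4%, 6% or 10% (assumed)
- share f of sICH patients who die without a scored rise = 0 to 30% (assumed)

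Formulas, with all N patients in the denominator: reported rate = s × (1 − f); missed cases = N × s × f.

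| s | f = 0 | f = 10% | f = 20% | f = 30% |
|---|---|---|---|---|
| 4% | 4.0% (0 missed) | 3.6% (12) | 3.2% (24) | 2.8% (36) |
| 6% | 6.0% (0) | 5.4% (18) | 4.8% (36) | 4.2% (54) |
| 10% | 10.0% (0) | 9.0% (30) | 8.0% (60) | 7.0% (90) |

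Worked cell: 6% × (1 − 0.30) = 4.2%; 3,000 × 0.06 × 0.30 = 54.

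**Step 4: does the denominator matter?** If unscored patients were also removed from the denominator, the rate would be s(1 − f)/(1 − sf). For s = 6% and f = 20% this is 0.048/0.988 = 4.86%, against 4.80%. Dropping them as missing therefore recovers almost none of the loss.

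**The case against.** The best case against the point has four parts.

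*The affected group is narrow.* Only patients who die of haemorrhage within 48 h with no repeat NIHSS at all are lost, and there may be none. This stands, and it is why the range starts at zero.

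*The clause carries the ECASS-III label and a reference, so it may abbreviate a fuller definition.* What the source says cannot be checked from the document, and nothing here relies on it. If the source covers death, the printed rule is an incomplete version of it; if it does not, the gap is real. The same edit settles both cases.

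*Early harm is visible elsewhere.* Deaths within 7 days are reported, intraparenchymal haemorrhage at 48 h is analysed without a stated NIHSS criterion, and on the mRS "a higher score means a worse outcome with 6 indicating death". This also stands: the registry as a whole does not hide early harm. But none of these outcomes changes who counts as sICH, and the mortality outcomes do not identify haemorrhage as the cause.

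*The committee would catch such cases.* It may, but its remit is controversial outcomes, and the article gives it no other sICH definition to apply.

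A reader might also infer that the same flaw affects NIHSS change, with the model run on survivors only and recovery overstated. The article does not say so. It states only "Change in the NIHSS score will be compared using a general linear model", and the general population rule is "Statistical analyses will be performed based on all enrolled participants or their legally authorized representatives who signed and did not withdraw informed consent". Nothing restricts the model to survivors. How deaths enter a secondary continuous outcome is commonly left to an analysis plan or full protocol, and neither is shown. Giving deaths a worst possible NIHSS score is a convention on which statisticians reasonably differ, so its absence is not an error.

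**Conclusion.** The point holds for sICH alone. As printed, the definition turns solely on an NIHSS rise and leaves out a fatal intracranial haemorrhage that was never scored. The direction of the error is known: the proportion can only be understated. Its size is not known. On the assumed figures, a true 6% would be reported as somewhere between 6.0% and 4.2%, with no loss at all if every fatal bleed had a rise scored first.

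It would be too broad to say that both NIHSS-based outcomes lose patients who die early. A patient whose rise was recorded before death is counted, deaths from other causes are rightly not sICH, and no survivor restriction on the NIHSS-change analysis appears in the text.

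The point is modest but worth acting on. A later analysis plan would normally inherit an outcome definition rather than rewrite it, so the wording should be corrected where it is set.

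**What to change.** Amend the definition in the Outcomes section to read, for example: *sICH is a rise of at least 4 NIHSS points, or death, caused by intracranial haemorrhage within 48 h*. Attribute death to haemorrhage from the material already collected: death reports, adverse event records, post-procedural and 24 h and 48 h imaging, and the central reading of event-related scans. Use the same definition for the logistic regression and for the Endpoint Events Assessment Committee.

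The cost is a short change to one sentence, with no new data collection. The reported sICH rate may become slightly less favourable, and a few deaths will need a judgement on cause. No change to the NIHSS-change analysis is requested on this ground.

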### Follow-up protocol

All included patients will have an in-person or telephone interview at the baseline, 24 ± 4 h, 48 ± 8 h, 7 ± 1 days, 12 ± 2 days or at discharge if earlier, and 90 ± 7 days post-EVT, respectively (Table 2). All data will be collected using electronic case report forms (eCRFs) and an online electronic data capture (EDC) system.

**Table 2 T2:** Timing of all procedures in DETECT-2.

**Time point**	**Screening**	**24 ±4 h**	**48 ±8 h**	**7 ±1 days**	**12 ±2 days**	**90 ±7 days**
**Enrollment**						
Eligibility screen	x					
Informed consent	x					
**Interventions**						
Intravenous thrombolysis	x					
Endovascular treatment	x					
**Clinical assessment**						
Diagnosis	x					
Head CT/MRI	x	x	x			
Cortical oxygen monitoring^a^		x				
TCD monitoring^b^		x				
NIHSS assessment	x	x	x	x	x	
mRS assessment	x					x
Medical history	x					
Demographic characteristics	x					
Vital signs	x	x	x	x	x	x
mTICI score	x					
TOAST classification					x	
**Laboratory examination**						
Blood routine	x					
Urine routine	x					
Coagulation	x	x	x		x	
Serum biochemistry	x				x	
ECG	x				x	
24-h ECG monitor				x		
**Follow-up record**						
Concomitant medications		x	x	x	x	x
Adverse events		x	x	x	x	x
Recurrent stroke and other vascular events		x	x	x	x	x

CT, computed tomography; MRI, magnetic resonance imaging; TCD, transcranial Doppler ultrasound; NIHSS, National Institutes of Health Stroke Scale; mRS, modified Rankin Scale; mTICI, modified thrombolysis in cerebral infarction; TOAST, Trial of Org 10172 in Acute Stroke Treatment; ECG, electrocardiogram.

^a^Continuous cortical oxygen monitoring was performed immediately after the endovascular treatment (monitoring 24 h).

^b^TCD monitoring was performed immediately, 6, 12, and 24 h after endovascular therapy.

### Data management, monitoring, and quality control

All patient data and case report forms will be entered in MedSci (http://DETECT2-China.medsci.cn). The data will be downloaded from MedSci with a dedicated person for statistical analysis. A third-party contract research organization (CRO) and the sponsor will audit the sites regularly to ensure adherence to study documentation, reporting procedures, and study protocol. The registry steering committee is comprised of external scientific advisors and will organize teleconference or in-person meetings to give recommendations about the study. Neuroradiologic assessment will be conducted in a core laboratory. Neuroimaging associated with clinical events will be collected centrally and interpreted by two independent neuroradiologists. An independent Endpoint Events Assessment Committee will adjudicate controversial clinical and imaging outcomes. The trial is initiated and supported by the Cerebrovascular Disease Collaboration and Innovation Alliance (CDCIA) of Liaoning.

### Sample size determination

According to a previous report (9), the proportion of functional independence at 90 days (mRS of 0–2) was 46% after EVT within 7 h of onset. After a two-sided test was performed with a power of 80% and an α set at 0.05, the calculated sample size is 1,565 cases. Considering a loss to follow-up rate of 25%, the sample size was therefore readjusted to 1,800 cases. Considering that patients with anterior circulation occlusion within 7 h of onset account for ~60% of the enrolled population, this registry has been designed to include 3,000 patients.

### Statistical analysis

Statistical analyses will be performed based on all enrolled participants or their legally authorized representatives who signed and did not withdraw informed consent. All data will be analyzed with SPSS 23.0 Software. The mean ± standard deviation (SD) will be used if continuous data are normally distributed, and the median and interquartile range (IQR) will be used if continuous data are non-normally distributed. Categorical data are expressed as a number (percentage). Differences between the primary endpoint and secondary endpoints such as mRS (0–1) at 90 days, the proportion of symptomatic intracranial hemorrhage at 48 h, the proportion of intraparenchymal hemorrhage at 48 h, and the occurrence of all-cause mortality at 7 days will be compared using binary logistic regression. The analysis will be adjusted for confounders, including age, sex, baseline NIHSS, pre-stroke mRS, prior stroke, baseline ASPECTS, site of arterial occlusion, transfer of patient, time from last known well, and IVT use (for EVT patients). The 90-day mRS score will be compared using ordinal logistic regression. Change in the NIHSS score will be compared using a general linear model. Time to events of stroke recurrence and other vascular events will be compared using Cox regression. Statistical tests are considered significant when the two-sided *P*-value is < 0.05.

The outcomes in DETECT2-China will be further analyzed by the following subgroups: (1) onset of symptoms to recanalization time (<7 vs. ≥7 h), (2) age (<65 vs. ≥65), (3) NIHSS score on admission (6–16 vs. ≥17), (4) baseline ASPECTS (<6 vs. ≥6), (5) thrombectomy technique (stent retriever vs. contact aspiration or other techniques), (6) anterior circulation vs. posterior circulation, (7) mean systolic blood pressure during the intervention (≤ 120 vs. >120 mmHg), (8) mechanical thrombectomy alone vs. bridging thrombectomy, (9) mothership vs. drip and ship models, (10) stroke etiology (ICAD vs. cardioembolic vs. others), and (11) use of general anesthesia vs. conscious sedation.

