## Limitations

As this is a prospective registry that enrolls only patients or their legally authorized representatives who provide consent, we may not be able to capture patients who do not or are unable to provide informed consent. Moreover, since this is a real-world registry study, other limitations are inevitable, including selection bias, a lack of standardization of techniques and treatment protocols, variability in operator experience, a heterogeneous patient population, and a lack of a control group.

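### The stated models name no center term or clustering method, although each of 30 centers follows its own EVT practice; precision may be overstated and technique contrasts may be mixed with center effects

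*Protocol article*

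**What the plan says.** Under Design, the registry "intends to include 30 comprehensive stroke centers", and under Sample size determination "this registry has been designed to include 3,000 patients". Under Intervention, "EVT will be carried out according to the usual practice of each center", with several devices and combinations allowed. The same section leaves the choice of anesthesia to the treating team for each patient.

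The Statistical analysis section assigns a model to each outcome type. Binary endpoints "will be compared using binary logistic regression". The 90-day mRS goes to ordinal logistic regression, NIHSS change to a general linear model, and recurrent stroke and vascular events to Cox regression. Ten confounders are named. Five concern demographics and prior or baseline clinical status, and the rest are "baseline ASPECTS, site of arterial occlusion, transfer of patient, time from last known well, and IVT use (for EVT patients"). The site in that list is the site of the occlusion, not the hospital. Center, operator and case volume are not named, and no random effect, stratification, GEE or robust variance appears anywhere in the article.

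The planned subgroup comparisons include "thrombectomy technique (stent retriever vs. contact aspiration or other techniques"), "mothership vs. drip and ship models", and general anesthesia against conscious sedation. The Discussion presents the pathway comparison as one of the things the registry will deliver. Limitations mentions unstandardized technique and "variability in operator experience", but the analysis section does nothing with either.

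**The concern.** Patients treated in one hospital share operators, work-up, devices and aftercare, so their outcomes tend to be correlated. Two separate consequences follow if center is left out.

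- **Precision.** With any positive ICC, the registry-wide proportion is less precise than a binomial calculation suggests. The same holds for the estimated effect of an exposure whose frequency varies between centers.
- **Confounding.** If centers that favor one technique also have better or worse results for other reasons, a single-level model assigns that difference to the technique. Patient-level adjustment does not remove it. The transfer covariate does not help either: it is close to being the pathway exposure itself and does not stand in for center.

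At stake are false claims that one technique or pathway is better, and an overstated certainty about the primary outcome.

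**Working it through.** **The plan's own figure.** The sample size section gives 1,565 before loss and 3,000 in total. The stated inputs (46%, two-sided 5%, 80% power) do not fix an N, because no difference is given. One assumed difference does match. For 46% against 51%, unpooled, n per group = (1.96 + 0.8416)² × (0.46×0.54 + 0.51×0.49) / 0.05² = 1,564.4, which rounds up to 1,565. Other assumed differences come close, so the basis cannot be identified. The section mentions no design effect. The 1,565 refers to anterior-circulation patients within 7 h, about 60% of the registry, so it is not the right denominator for the registry-wide proportion.

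**Inputs.** From the article: 30 centers, 3,000 patients, 25% loss, 46%. Assumed: ICC of 0.01 to 0.05, and centers of equal size.

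- Evaluable patients: 3,000 × 0.75 = 2,250, so m = 2,250/30 = 75 per center.
- Design effect: DE = 1 + (m − 1) × ICC = 1 + 74 × ICC.
- Half-width under independence: 1.96 × √(0.46 × 0.54 / 2,250) = 2.06 points; with clustering, 2.06 × √DE.
- True error of a nominal 5% test when the exposure is wholly determined by center: 2 × [1 − Φ(1.96/√DE)].

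| Assumed ICC | DE | Effective N (2,250/DE) | Half-width (points) | True error, wholly center-determined exposure |
|---|---|---|---|---|
| 0 | 1.00 | 2,250 | 2.06 | 5% |
| 0.01 | 1.74 | 1,293 | 2.7 | 14% |
| 0.02 | 2.48 | 907 | 3.2 | 21% |
| 0.05 | 4.70 | 479 | 4.5 | 37% |

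The assumed loss matters little. With all 3,000 evaluable (100 per center), the half-width goes from 1.78 to between 2.52 and 4.35 points.

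**Less extreme exposures.** A simulation used 30 centers of 100 patients, a true odds ratio of 1 and no other covariates, with 300 replicates per setting (Monte Carlo standard error about 1.3 percentage points at 5%). The ICC was set on the log-odds scale at 0.01 / 0.02 / 0.05. Strongly center-dependent means that the center log-odds of exposure has an SD of 2: centers one SD either side of the average use the technique in about 12% and 88% of patients. The model without center gave:

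| Exposure | Type I error | Mean odds ratio |
|---|---|---|
| Same mix in all centers | 0.05 / 0.06 / 0.07 | about 1 |
| Strongly center-dependent, unrelated to center outcome | 0.12 / 0.11 / 0.24 | about 1 |
| Wholly center-determined, unrelated to center outcome | 0.17 / 0.22 / 0.40 | about 1 |
| Strongly center-dependent, correlated 0.5 with center outcome | 0.32 / 0.54 / 0.80 | 1.11 / 1.16 / 1.27 |

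Center fixed effects brought the second and fourth rows back to an odds ratio of about 1.00 and an error of 0.03 to 0.06. They cannot be used for a wholly center-determined exposure.

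**The case against.** The strongest reply is that this is silence in a condensed article. The article never says that patients are treated as independent, its confounder list is introduced as open-ended, and an analysis plan that is not shown could add center. That is fair as far as it goes. But the article names a model for each outcome and ten specific confounders. As written these are single-level models, and an open covariate list does not supply a variance method. The factor left out is also the one that the Intervention section says governs practice.

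Other parts of the reply stand and limit the point:

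- A reader might infer that technique, anesthesia and pathway are all center-level exposures. The article does not support this. Anesthesia is chosen case by case, and nothing shows that a center receives only direct or only transferred patients. Technique is the one tied to center practice, and even there each center may use several approaches.
- A reader might infer that the contrasts are confounded. That requires exposure to be related to a center's outcome level, which the article does not show. In the simulation, center-dependent exposure without that relation inflated the error but left the odds ratio unbiased.
- A reader might infer that reported confidence intervals will be too narrow. The article mentions P-values and no confidence intervals, so the half-widths above illustrate lost precision and do not correct a stated figure.

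**Conclusion.** The point holds as a risk that the stated analysis leaves uncontrolled. The named models and covariates have no center term or clustering method in a 30-center registry whose practice is set locally and whose planned contrasts include technique and pathway. Standard errors and P-values may overstate precision, and contrasts with an uneven mix across centers may carry center effects.

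For the overall proportion, the loss is from about 2.1 to between 2.7 and 4.5 points of half-width. This assumes an ICC of 0.01 to 0.05, which the article does not give, equal centers and 25% loss. The 14% to 37% error rate is a worst case for an exposure wholly fixed by center and should not be read as the expected error of the planned contrasts. Where the exposure mix is similar across centers, the error stays near nominal. The change should be made, since it is cheap and the technique contrast is exposed.

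**What to change.** State in the analysis plan:

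1. Binary, ordinal and linear models include a center effect (random intercept or fixed effect), or use GEE or cluster-robust variance by center.
2. The Cox model uses stratification by center, shared frailty or robust variance.
3. The primary proportion is reported with a cluster-robust 95% interval.
4. For technique and pathway, the within-center effect is reported, through center fixed effects or by adding the center mean of the exposure. Robust variance alone corrects the standard error but not confounding by center, so items 1 and 4 do different jobs.
5. The share of each technique and pathway by center is tabulated, so that readers can see how far each contrast can be made within centers.

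The cost is a few sentences of analysis text, slightly more analysis work and somewhat wider intervals. No new data are needed, because the treating center should already be identifiable in a multi-center data capture system whose sites are audited. Patient numbers and clinical procedures do not change.
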